## Abstract

**Background:**

Compared to those in higher socioeconomic groups, diabetic patients in lower socioeconomic groups have less favourable metabolic control and experience more diabetes-related complications. They encounter specific barriers that hinder optimal diabetes self-management, including a lack of social support and other psychosocial mechanisms in their immediate social environments. *Powerful Together with Diabetes *is a culturally sensitive social network intervention specifically targeted to ethnic Dutch, Moroccan, Turkish, and Surinamese diabetic patients in lower socioeconomic groups. For ten months, patients will participate in peer support groups in which they will share experiences, support each other in maintaining healthy lifestyles, and learn skills to resist social pressure. At the same time, their significant others will also receive an intervention, aimed at maximizing support for and minimizing the negative social influences on diabetes self-management. This study aims to test the effectiveness of *Powerful Together with Diabetes*.

**Methods/Design:**

We will use a quasi-experimental design with an intervention group (Group 1) and two comparison groups (Groups 2 and 3), N = 128 in each group. Group 1 will receive *Powerful Together with Diabetes*. Group 2 will receive *Know your Sugar*, a six-week group intervention that does not focus on the participants' social environments. Group 3 receives standard care only. Participants in Groups 1 and 2 will be interviewed and physically examined at baseline, 3, 10, and 16 months. We will compare their haemoglobin A1C levels with the haemoglobin A1C levels of Group 3. Main outcome measures are haemoglobin A1C, diabetes-related quality of life, diabetes self-management, health-related, and intermediate outcome measures. We will conduct a process evaluation and a qualitative study to gain more insights into the intervention fidelity, feasibility, and changes in the psychosocial mechanism in the participants' immediate social environments.

**Discussion:**

With this study, we will assess the feasibility and effectiveness of a culturally sensitive social network intervention for lower socioeconomic groups. Furthermore, we will study how to enable these patients to optimally manage their diabetes. This trial is registered in the Dutch Trial Register: NTR1886

## Background

Lower socioeconomic (SE) groups are not only disproportionately affected by type 2 diabetes, they also have more diabetes-related complications and higher diabetes-related mortality compared to diabetic patients in higher SE groups [1-3]. A possible explanation for this could be poorer glycaemic control. Achieving optimal glycaemic control requires the diabetic patient to take part in a complex set of tasks: adhere to dietary advice and medications, engage in regular physical activity, quit smoking, and monitor blood glucose levels, known as diabetes self-management (DSM) [4]. These tasks seem to be more challenging for diabetic patients in lower SE groups [5-7].

Interventions aimed at improving DSM can contribute to better glycaemic control and the prevention of diabetes-related complications [8,9]. However, there are indications that interventions for the general diabetic population are less suitable for lower SE groups and need to be adapted to the specific barriers they face [10,11]. Barriers to DSM among lower SE groups include a lack of knowledge of diabetes, low self-efficacy, low perceived control, and low health literacy [5,7,12].

Another mentioned barrier to DSM among lower SE groups is a lack of diabetes-related social support [13-15]. To maintain lifestyle changes, long-term social support in particular seems beneficial [13,16]. From other fields such as sociology we know that social support is not the only psychosocial mechanism through which the immediate social environment influences health [17-19]. Other psychosocial mechanisms are social influence such as peer pressure, norms and social comparison processes, which extend from the social network's values and norms, and social engagement which defines and reinforces meaningful social roles through network participation [20]. These psychosocial mechanisms may have both negative and positive effects on health behaviour [17]. For example, if the social norms in the immediate social environment are incongruent with DSM, family and/or friends might hinder DSM (intentionally or unintentionally) by providing negative role models or by exerting peer pressure [17,20,21].

Patients in lower SE groups are often surrounded by social networks that seem to have a strong adverse effect on their DSM. These groups often have small, dense social networks with strong ties that consist primarily of people in similar (low SE) situations to their own, mainly family members and close friends [18]. Their social networks often lack more distant acquaintances, that is, people who move in different circles than their own. These distant acquaintances are needed to introduce resources, information, and ideas that might be missing from their own social networks (such as diabetes related information and role models). These 'closed' social networks are known to impose strong group norms on their social network members [18,20]. Combined with the unfavourable diabetes outcomes among lower SE groups, this may suggest that these groups are confronted with strong psychosocial mechanisms (social support, social influence and social engagement) in their immediate social environments that adversely affect their DSM. This is supported by recent studies which show that lower SE groups experience difficulties in coping effectively with psychosocial mechanisms such as peer pressure, cultural expectations, fewer positive role models, and not having control over their family's lifestyle choices [22-24].

To improve DSM among lower SE groups, it seems important to focus specifically on creating long-term diabetes-related social support, and to target the other existing psychosocial mechanisms such as social influence and social engagement in their immediate social environments that have adverse effects on their DSM. Therefore, we systematically developed a theory-based culturally sensitive social network intervention targeted to ethnic Dutch, Turkish, Moroccan, and Surinamese diabetic patients in lower SE groups. *Powerful Together with Diabetes *(PTWD) aims to improve DSM by stimulating long-term social support and targeting existing psychosocial mechanisms in the immediate social environment that have an adverse effect on DSM. This paper describes the intervention, the theoretical background of this intervention, and the study design.

## Methods/Design

### The intervention: *Powerful Together with Diabetes (PTWD)*

To develop PTWD, we used the intervention mapping method: a systematic approach for designing and evaluating health-promotion interventions. The first step in intervention mapping is a needs assessment, followed by creating matrices of change objectives, selecting theory-informed intervention methods and practical strategies, and finally, producing programme components and materials [25].

For the needs assessment, we examined the existing literature for barriers to DSM among lower SE groups. We also held semi-structured qualitative interviews with diabetic patients (n = 21), analysed the content of an internet forum for diabetic patients, and observed the daily practices of a diabetic nurse in a neighbourhood with low socioeconomic status for two days. We created matrices of change objectives with the help of researchers specialized in intervention mapping. When selecting theory-informed intervention methods and practical strategies and producing programme components and materials, we examined the existing literature and currently ongoing lifestyle interventions for methods and strategies that would fit our target population. We also submitted our practical strategies and programme components twice to a panel of experts with Turkish, Moroccan, and Surinamese backgrounds (n = 6), and consulted them individually with specific questions about the different cultural groups in our target population. Finally, we pretested some of our intervention components among the target population using focus group discussions (n = 3).

Because this intervention has to stimulate long-term social support and target existing psychosocial mechanisms in DSM, PTWD will consist of the following three components: 1) group meetings for diabetic patients, 2) group meetings for the participants' significant others (e.g. family and/or friends), and 3) social network therapy sessions with the diabetic patient and his/her significant other(s). PTWD will last ten months and consist of two phases (see Table 1).

**Table 1 T1:** Overview of the two phases of *Powerful Together with Diabetes*

Phase 1 (months 1-3)	Phase 2 (months 4-10)
Thirteen weekly peer group meetings for diabetic patients. Three group meetings for significant others.	Eight twice-monthly peer group meetings for diabetic patients followed by five monthly peer group meetings. Three group meetings for significant others. Two social network therapy sessions for the diabetic patient and his/her significant other(s).

The intervention will be held in the mother tongue of the participants. We culturally targeted PTWD by changing the outline of the intervention to make it compatible with the ethnic minority participants' annual visits to their countries of origin and the celebration of Ramadan. We also culturally tailored the content of the intervention components to the different cultural groups, for example, by incorporating sociocultural values and barriers to DSM, and adapting the materials to fit the needs of the different cultural groups.

We describe the intervention components below, including their behavioural goals and the determinants we addressed to achieve these goals. The behavioural goals were based on the theory of self-regulation, different self-management theories, and the transactional model of stress and coping, relapse prevention, and social learning theories [26-30]. Because targeting psychosocial mechanisms within the immediate social environment of the participants (such as the exchange of social support) plays an important part in this intervention, for every intervention component we also created separate behavioural goals for these determinants.

#### Group meetings for diabetic patients

The diabetic patients will participate in group meetings (ten persons per group) for ten months. In Phase 1 (months 1-3), the participants will be provided with the basic 'tools' they need to manage their diabetes. This phase focuses on creating positive outcome expectations [26,31] and moral norms [28,32], increasing knowledge, skills [26], and self-efficacy [26,31], stimulating social support [33], and recognizing and dealing with psychosocial mechanisms that hinder optimal DSM, such as peer pressure and existing social norms [20,31]. In Phase 2 (months 4-10), the participants will learn how to put the tools they gathered in Phase 1 to use. They will develop and train DSM skills until they have a solid set of coping skills [28,29,34], which will enable them to optimally manage their diabetes in the long term.

To reach these behavioural goals and change the determinants associated with them, we chose strategies that would fit our target population and their specific needs regarding information processing. For example, by engaging the participants in an interactive diabetes quiz, we aim to increase their practical knowledge about diabetes. We aim to increase DSM skills and self-efficacy through a 'letter of the week', in which a fictitious diabetic patient presents a problem and asks the group members for advice. To increase awareness about barriers to DSM (Phase 2), the participants will monitor their own behaviour with the help of specially designed diaries. Through participatory problem-solving and rehearsal situations, we aim to improve the participants' skills and self-efficacy to overcome these barriers. Due to the large number of behavioural goals, in Additional files 1 and 2 we present a representative summary of the behavioural goals, the determinants addressed, and the strategies used in Phases 1 and 2.

Stimulating long-term social support and targeting existing psychosocial mechanisms that have an adverse effect on DSM are important parts of the intervention. Examples of strategies used to stimulate social support are interactive games in which the participants complement each other on their DSM and other subjects (self-affirmation), and stimulating the exchange of advice between participants. The participants are also encouraged to see each other outside of the group meetings, and to undertake DSM-related activities together (e.g. participating in an exercise initiative in the neighbourhood). A final aim of the intervention is that the participants will continue to see and consult each other after the intervention has ended.

To stimulate social support and target existing psychosocial mechanisms that have an adverse effect on DSM in participants' immediate social environments, we use role-model stories, rehearsal situations, and homework assignments that focus on these behavioural goals. In addition, the group meetings for the significant others and the social network therapy sessions (see below) will contribute to the achievement of this behavioural goal.

#### Group meetings for significant others

Each diabetic patient will identify one or two persons in his/her immediate environment with a great deal of influence on his/her DSM. These significant others will participate in six group meetings with other significant others: three during Phase 1 and three during Phase 2. The diabetic patients will not be present during these meetings.

In Phase 1, we will aim to increase the significant others' knowledge about diabetes and its treatment, make them feel that DSM is necessary and inevitable (outcome expectations and perceived cultural norms), and that they have an important role in the DSM of their relative/friend (perceived cultural norms and self-efficacy). To increase the significant others' knowledge, we will use a short version of the interactive diabetes quiz (which we use in the group meetings for the diabetic patients). Using positive role-model stories and shared positive experiences from group members (vicarious reinforcement) and group discussions, we will try to increase positive outcome expectations and positive moral norms towards DSM, and increase awareness about the role of significant others in the DSM of diabetic patients.

In Phase 2, we will focus on supporting their relative/friend in managing his/her diabetes. We will aim to make the significant others aware of the fact that DSM is a shared responsibility. Next, we will aim to make them feel confident they can support the diabetic patient with his/her DSM (self-efficacy) and be able to effectively support the diabetic patient in his/her DSM (skills). By exchanging positive experiences and through communication skills training combined with rehearsal situations and feedback, we will aim to improve the significant others' skills and self-efficacy (see Additional file 3). The group meetings will be followed by the social network therapy sessions.

#### Social network therapy sessions

In Phase 2, the diabetic patient and his/her significant other(s) will take part in two social network therapy sessions. With these sessions, we will aim to further stimulate the exchange of social support and diminish negative social influences on DSM. In these sessions, the group leader will lead a discussion between the diabetic patient and his/her significant other(s). In the first meeting, they will discuss the ways the diabetic patient is currently managing his/her diabetes and how his/her DSM could be improved. Next, they will discuss the ways the significant other(s) can assist the diabetic patient in improving his/her DSM. Finally, they will make an action plan to put the things discussed into action. In the second meeting, this action plan will be evaluated and further refined (see Additional file 4).

### Intervention for the comparison group: *Know your Sugar*

To evaluate the effects of an extra focus on psychosocial mechanisms and social support in the intervention group, we chose to offer the comparison group a lifestyle group intervention as well. *Know your Sugar *(KYS) is a group intervention that aims to provide the participants with the information they need to be able to manage their diabetes, and provide them with the opportunity to exchange social support. KYS will not actively focus on social support and the pre-existing psychosocial mechanisms that influence DSM in the participants' immediate social environments.

KYS consists of six weekly group meetings. It is based on 'How to deal with diabetes', a Dutch course originally developed for Turkish diabetic patients, and Dutch National Institute for Health Promotion and Disease Prevention (NIGZ) posters (i.e. large visual aids used by diabetic nurses to facilitate explaining and talking about diabetes-related subjects with patients). Both are known as the current best practices in the Netherlands for diabetic patients in lower SE groups. Together they form the foundation of KYS, which we then further developed to make it culturally sensitive for the different cultural groups in our study population. To increase the participants' knowledge, we will use the same strategies we use in PTWD, but with no extra focus on the exchange of experiences and social support.

#### Training and supervision of group leaders

PTWD and KYS will be given by different group leaders. The PTWD group leaders will receive a four-hour training prior to Phase 1 and a four-hour training prior to Phase 2. The KYS group leaders will receive a two-hour training prior to the intervention. During the interventions, all group leaders will have regular contact with the researchers by telephone. During these calls they can ask questions about the intervention and get practical advice.

### Research questions

This study will aim to answer the following research questions:

1. What are the effects of the intervention (PTWD) on haemoglobin A1C (HbA1c) compared with the intervention for the comparison group (KYS) and standard care at 3, 10, and 16 months?

2. What are the effects of the intervention on diabetes-related quality of life compared with the intervention for the comparison group at 3, 10, and 16 months?

3. What are the effects of the intervention on health-related outcome measures, diabetes self-management, and intermediate outcome measures compared with the intervention for the comparison group at 3, 10, and 16 months?

4. What is the feasibility of the intervention and the intervention for the comparison group?

5. What is the cost-effectiveness of the intervention compared with the intervention for the comparison group and standard care?

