#### Data collection (procedure of effect evaluation and process evaluation)

Data collection will take place at baseline (T0), after 3 months (T1), after 10 months (T2), and after 16 months (T3) for both the intervention group (PTWD) and the comparison group (KYS). At T1 we will only administer a short structured interview aimed to measure knowledge and DSM. At T0, T2, and T3 we will administer a structured interview and a physical examination. We will study the participants' medical records at all data collection moments. The HbA1c levels of 128 patients who receive standard care will be collected from a large database owned by a GP collective in the Netherlands. See Figure 1 for an overview of the measurements in this study.

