#### Blood and urine samples

In the Netherlands, HbA1c levels and fasting plasma glucose of diabetic patients are measured every three months. An extensive analysis of blood and urine samples is performed at least once a year [39]. For T0, T2, and T3, we will collect these data from the participants' medical records. More specifically, we will collect:

• Fasting plasma glucose, HbA1c, total cholesterol, high-density lipoprotein (HDL) cholesterol, triglycerides, creatinine, and creatinine clearance, glomerular filtration rate calculated according to the Modification of Diet in Renal Disease Study (MDRD equation)

• Microalbuminuria

In addition, we will use medical records to collect information on the participants' medication use and diabetes-related complications: retinopathy, cataract, kidney failure, microalbuminuria, myocardial infarction, angina pectoris, transient ischaemic attack (TIA), cerebrovascular accident (CVA), claudicatio intermittens, diabetic ulcers, amputation, polyneuropathy, and sensitivity problems in the feet.

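### Research questions 1 to 3 ask for 3-month effects, but quality of life and most other outcomes are not measured then, and the sections conflict on HbA1c

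*Protocol article*

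**What the plan says.** **Research questions.** All three effect questions name the same follow-up times. HbA1c is to be "compared with the intervention for the comparison group (KYS) and standard care at 3, 10, and 16 months". The second question reads "What are the effects of the intervention on diabetes-related quality of life compared with the intervention for the comparison group at 3, 10, and 16", counted in months. The third covers "health-related outcome measures, diabetes self-management, and intermediate outcome measures compared with the intervention for the comparison group at 3, 10, and 16 months".

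**Data collection.** T0 is baseline, and T1, T2 and T3 fall at 3, 10 and 16 months. For T1 the text is restrictive: "At T1 we will only administer a short structured interview aimed to measure knowledge and DSM". The structured interview proper and the physical examination are assigned to T0, T2 and T3. The same paragraph says the researchers will study participants' "medical records at all data collection moments".

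**Physical examination.** This section repeats T0, T2 and T3 for weight, height, waist, hip, blood pressure and heart rate.

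**Blood and urine samples.** HbA1c and fasting plasma glucose are said to be measured every three months in Dutch routine care. The extraction sentence then reads "For T0, T2, and T3, we will collect these data from" the medical records, and the list that follows includes HbA1c.

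**Abstract, Methods/Design.** "Participants in Groups 1 and 2 will be interviewed and physically examined at baseline, 3, 10, and 16 months".

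**The concern.** The questions promise 3-month comparisons that the measurement schedule does not support. Quality of life matters most here, because the section on primary and secondary outcome measures names it as a primary outcome alongside HbA1c.

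HbA1c raises a different problem. Depending on which section the field staff follow, each participant in the two intervention arms contributes either three or four HbA1c values (T0, T2, T3, with or without T1). The Statistical analyses section uses generalized linear mixed models to follow individual change over time, so the number of repeated values is an input to that model. If the text stays unresolved, whether T1 enters could be settled after data have been seen, or could differ between practices.

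Three months is also the end of Phase 1 of *Powerful Together with Diabetes* and the only planned follow-up before Phase 2. A reader of the research questions would expect an early-effect estimate there.

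**Working it through.** No sample size, power or error rate enters this point, so the check is a cross-tabulation. Each outcome in the research questions is taken from the section on primary and secondary outcome measures and set against the schedule in Data collection, Physical examination, and Blood and urine samples.

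| Outcome asked for at 3 months | Source of the data | Scheduled at T1? |
|---|---|---|
| HbA1c (question 1) | Medical records | Yes under Data collection; T1 not listed under Blood and urine samples |
| Diabetes-related quality of life (question 2) | Questionnaire in the structured interview (Table 2) | No |
| Blood pressure, heart rate, weight, waist, hip (question 3) | Physical examination | No; the abstract says yes |
| Lipid profile (question 3) | Medical records | Same conflict as HbA1c |
| Self-management apart from BMI (question 3) | T1 interview or records | Yes |
| BMI, listed under self-management (question 3) | Weight and height from the physical examination | No |
| Knowledge (question 3) | T1 interview | Yes |
| The other intermediate outcomes (question 3) | Full structured interview | No |

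**Count of intermediate outcomes.** The list is depression, attitude, knowledge, self-efficacy, coping skills, social networks (size and composition), social support, social influence and social engagement: nine in all. The T1 interview covers knowledge only, so 9 − 1 = 8 have no 3-month measurement.

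**Physical examination.** Two body sections (Data collection and Physical examination) agree on T0, T2 and T3. Only the abstract adds 3 months, so the abstract is the statement out of line.

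**HbA1c.** If records are studied at every time point, a T1 value is within reach. The section devoted to laboratory data nevertheless names three time points and leaves T1 out. The two statements point different ways, and neither refers to the other. For the standard-care group, Data collection says HbA1c comes from a GP collective's database but does not say for which time points, although question 1 asks for a 3-month comparison with that group too.

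**Other time points.** At 10 and 16 months, each of these outcomes has a scheduled source in the two intervention arms. The mismatch is confined to 3 months, apart from the abstract's wording.

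**The case against.** The strongest reply is that little turns on this. Both primary outcomes are set at 16 months, the sample size rests on HbA1c at 16 months, and all the outcomes in questions 2 and 3 are scheduled at T2 and T3. The phrase naming 3, 10 and 16 months may simply have been carried from one question to the next. That is fair, and it limits the weight of the point. It does not remove the mismatch, because the text still asks for an effect on a primary outcome at a time when that outcome is not collected.

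A reader might infer that HbA1c is definitely not collected at 3 months. The documents do not support that. The laboratory section lists T0, T2 and T3 but does not say these are the only times, and Data collection has the records studied at T1. With routine measurement every three months, a value near T1 could well be retrievable. This is a conflict to resolve, not an established absence.

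A reader might also infer that lipid values will often be missing at T2 or T3, since the extensive panel is described as done at least yearly and those visits are six months apart. That frequency is a minimum, and the actual testing frequency is not given. Separate values are not assured, but no rate of missingness follows.

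Figure 1, the measurement overview, is not shown. It might favour one version for HbA1c, but it could not make the research questions, the abstract and the body sections agree.

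Finally, a condensed article may leave detail to a fuller document. Here the time points are stated, and they are incompatible as stated.

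**Conclusion.** The point holds for the 3-month comparisons and should be corrected.

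- **Quality of life:** the 3-month part of question 2 cannot be answered under the stated schedule.
- **Question 3:** the physical-examination outcomes, BMI and eight of nine intermediate outcomes have no 3-month measurement. Knowledge and the self-management items from interview or records do.
- **HbA1c:** the sections conflict on whether a 3-month value is extracted.
- **Abstract:** its 3-month physical examination is contradicted by two body sections.

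It would be wrong to read this as a threat to the trial's main conclusion: the 16-month primary comparison and the sample size do not depend on T1. The conclusion rests on taking the word *only* in the T1 sentence at face value, and on BMI being derived from the measured weight and height.

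**What to change.** 1. In Blood and urine samples, add T1 to the extraction of HbA1c and fasting plasma glucose, so that this section agrees with Data collection and with question 1.
2. In Data collection, state that the corresponding 3-month HbA1c value for the standard-care group will be taken from the GP database.
3. Limit question 2 to 10 and 16 months.
4. Limit question 3 at 3 months to knowledge and to self-management items obtained by interview or from records. Exclude BMI explicitly, because it is listed under self-management; a restriction to self-management as a whole would leave the same gap.
5. Correct the abstract so that it does not claim a physical examination at 3 months.

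The cost is text changes, plus a T1 extraction of HbA1c and fasting glucose from records that Data collection already has the team studying then, and a matching 3-month HbA1c extract from the GP database. No extra visit or test is needed. The downside is that some 3-month claims are given up.
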